### Study procedures

2.3.

The study is organized into five scheduled clinic visits and two phone calls as outlined in Table 2. Additional visits are arranged if necessary. At baseline visit, demographics (age, sex, race), past medical history, and anthropometric measurements (height, weight) are collected. The EuroQol EQ-5D-3L questionnaire is used to evaluate five aspects of health-related quality of life (mobility, self-care, usual activities, pain/discomfort, and anxiety/depression) at baseline, visit 4 and visit 5.

**Table 2 T2:** Study visits and procedures.

Visit	Washout	1	2	3		4		5
Week	−2	0	4^a^	8^a^	12^a^	26^a^	38^a^	52
Informed consent taking	×^b^	×^b^			Phone call follow-up		Phone call follow-up	
Demographics and anthropometrics collection	×^b^	×^b^						
Collection of past medical history, including medications	×^b^	×^b^						
Urine pregnancy test	×	×	×	×		×		×
Randomization		×						
Health-related quality of life assessment		×				×		×
Study medication dispense		×	×	×		×		
Medication adherence check		×	×	×		×		×
Blood collection for renal function and potassium level		×	×	×		×		×
Blood collection for hematocrit		×						×
Blood collection for storage		×						×
Office blood pressure measurement		×	×	×		×		×
24-h ambulatory blood pressure monitoring		×	×	×		×		×
Cardiovascular magnetic resonance		×						×
Adverse events evaluation		×	×	×		×		×

^a^
Additional clinic visits are arranged if necessary.

^b^
These procedures are only done once, either at the washout visit or visit 1.

#### Urine pregnancy test

2.3.1.

Women who are not pregnant at enrollment but are otherwise of child-bearing potential will undergo urine dip-stick pregnancy test at each study visit. A positive urine pregnancy test would require study drug discontinuation and participant’s withdrawal from the study.

#### Blood pressure measurement

2.3.2.

A correctly sized cuff of the OnTrak 90277 device (Spacelabs Healthcare, Snoqualmie, WA, USA) is applied to the participant’s non-dominant arm. Over 24 h, automated out-of-clinic blood pressure measurements are taken at intervals of 20 min from 6 AM to 10 PM and 30 min from 10 PM to 6 AM the following day. Instruction and demonstration on the device usage are given to the participants by the clinical research coordinator.

#### Blood collection and storage

2.3.3.

Serum creatinine and potassium levels are measured at all visits as part of safety monitoring. Additional serum and plasma are collected and stored in aliquots at −80°C for future evaluation of circulating biomarkers pertaining to RAAS activity, myocardial fibrosis (including pro-fibrotic mediators and parameters assessing cardiac extracellular matrix turnover), and injury. This will be explored and reported in a separate circulating biomarkers sub-study.

#### Cardiovascular magnetic resonance imaging

2.3.4.

##### Image acquisition

2.3.4.1.

All CMR scans are performed using a standardized imaging protocol on the Siemens Aera 1.5 T scanner (Siemens Healthineers, Erlangen, Germany). Long-axis balanced steady-state free precession cine images are acquired in the two-, three-, and four-chamber views (acquired voxel size 1.6 × 1.3 × 8.0 mm; 30 phases per cardiac cycle). Short-axis cines extending from the mitral valve annulus to the apex are also acquired (acquired voxel size 1.6 × 1.3 × 8.0 mm; 30 phases per cardiac cycle).

Diffuse interstitial myocardial fibrosis is assessed by myocardial T1 mapping using the modified Look-Locker inversion-recovery sequence. Native T1 map is acquired using a heartbeat scheme of 5(3)3; post-contrast T1 map is acquired 15 min after administration of 0.1 mmol/kg of gadobutrol (Gadovist; Bayer Pharma AG, Germany) using a heartbeat scheme of 4(1)3(1)2.

##### Image analysis

2.3.4.2.

All images are de-identified and analyzed at the National Heart Research Institute (NHRIS) CMR Core Lab by trained personnel blinded to trial data, including treatment allocation and blood pressure values.

Analysis of LV mass, volumes, and function (including multi-directional myocardial strain) is performed using standardized protocols (17, 23). ECV fraction is calculated using the T1 mapping module in cvi42 image analysis software (Circle Cardiovascular Imaging, Calgary, Canada) (24). Interstitial volume (indexed to body surface area) is derived from ECV × myocardial volume, where myocardial volume (mL) is defined as myocardial mass(g)/1.05 g/mL. Hematocrit for calculating ECV is taken on the day of CMR.

#### Adverse events evaluation

2.3.5.

At each clinic visit, adverse events related to study treatment and/or procedures are assessed. If present, they will be recorded and reported to the local ethics board and Health Sciences Authority (the local governing body which oversees clinical trials) within the stipulated timeframe.

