**Figure 1 F1:**
[figure not shown]
Recruitment, randomization, and treatment protocol. ACEi, angiotensin-converting enzyme inhibitor; ARB, angiotensin II receptor blocker; LV, left ventricular; LVH, left ventricular hypertrophy; Δ, change.

Participants are randomized on an allocation ratio of 1:1 to either sacubitril/valsartan or valsartan without blinding. Randomization service is provided by the Singapore Clinical Research Institute (SCRI) in closed, opaque, and sequentially numbered envelopes. Research member who measures CMR endpoints is blinded to treatment allocation and clinical details including blood pressure values.

The treatment duration is 52 weeks, with the same target systolic blood pressure for both treatment groups which is less than 140 mmHg according to contemporary guidelines at the time of study conception (21, 22). The initial dosage of sacubitril/valsartan is 100 mg–200 mg/day and can be titrated up to a maximum dose of 400 mg/day. The initial dosage of valsartan is 80 mg–160 mg/day and can be titrated to a maximum dose of 320 mg/day. Medications are titrated to the maximum dose tolerated by the participants. If the study medications are inadequate for optimal blood pressure control, additional non-RAAS inhibiting anti-hypertensive agents are prescribed. Study medications are dispensed by a pharmacist at NHCS. Treatment compliance is monitored by pill counting at each clinic visit.

Participants may withdraw from the study at any time. Withdrawal can be initiated and documented by the investigator if continuation would be detrimental to the participant’s well-being. If withdrawal happens after more than 12 weeks of randomized treatment, all endpoint investigations will be performed at the time of withdrawal (unless participant is not contactable, refused, or deceased). The first participant was recruited on 19 June 2019.

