### Design

3.2.

This trial is conducted in a PROBE design that is more reflective of real-world clinical practice, less costly whilst delivering the advantages of classic double-blinded studies (30). Although a double-blinded design is maximally robust with respect to bias, it requires the commercial production of blinded medications and also adds difficulty to titration of medications as treating clinicians are blinded from the medication allocation and dosages. A PROBE study design, used in many hypertension trials, involves treatment known to participants and clinicians as in standard care practice, enables scientific investigation with stringent randomization, and eliminates bias with blinded endpoint evaluation.

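### Section 2.3.5 as written confines adverse-event recording to events judged related to treatment or procedures, in an open-label trial that names no blinded adverse-event assessor

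*Protocol article*

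**What the plan says.** Section 2.3.5 of the protocol article has two sentences on adverse events. The first sets what is looked for: "At each clinic visit, adverse events related to study treatment and/or procedures are assessed". The second sets what happens next: "If present, they will be recorded and reported to the local ethics board and Health Sciences Authority", by the required deadline.

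Other parts of the article bear on this:

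- **Table 2 (Section 2.3)** has a row labelled "Adverse events evaluation", marked at visits 1 to 5. The row carries no restriction to related events.
- **Section 2.2** says that participants are allocated "to either sacubitril/valsartan or valsartan without blinding". The blinding it describes is for imaging: "Research member who measures CMR endpoints is blinded to treatment allocation and clinical details including blood pressure values".
- **Section 3.2** says that the design "involves treatment known to participants and clinicians as in standard care practice".
- **Section 2.3.3** provides safety data that need no attribution: "Serum creatinine and potassium levels are measured at all visits as part of safety monitoring".
- **Section 2.4.2** names comparisons of the arms at baseline and on CMR changes. It names no adverse-event comparison.

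**The concern.** Recording what happened and judging why it happened are two separate steps. Section 2.3.5 as written merges them: relatedness is the condition for being assessed, and therefore for being recorded. Two consequences follow.

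First, an event wrongly judged unrelated does not enter the adverse-event record. It cannot be reclassified later when a pattern appears, and it cannot be counted by arm.

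Second, attribution is a matter of opinion, and here it is probably formed by people who know the drug. If the threshold for calling an event related differs between the arms, recorded rates can differ when true rates do not, or agree when true rates differ. The blinded CMR reading protects the imaging endpoints but does not extend to adverse events.

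What is at stake is the credibility of any safety table by arm. The efficacy conclusion is not at stake.

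**Working it through.** **1. Is there a figure to reproduce?** The article states no adverse-event rate, safety endpoint or safety sample size. Its one computed figure, the sample size in Section 2.4.1, does not depend on this point. It does reproduce: SD of change = 5.8 × √(2 × (1 − 0.60)) = 5.19 mL/m², which for a difference of 3.5 mL/m² gives 35 per group and 80.6% power.

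**2. Reading the texts together.**

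| Question | What the article gives |
|---|---|
| Which events are assessed? | Related ones (2.3.5, first sentence); no limit in the Table 2 row |
| Which events are recorded? | "If present, they will be recorded and reported to the local ethics board and Health Sciences Authority": the pronoun refers back to the related events |
| Does any sentence record events regardless of cause? | None found |
| Who judges relatedness? | Not stated |
| Who is blinded? | Only those measuring CMR endpoints are described as blinded (2.2, 2.3.4.2) |
| Who knows the drug? | Participants and clinicians (3.2) |

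The only explicit rule is therefore the narrow one. Table 2 does not overturn it, because a row label gives no definition, but the two do not match.

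**3. What could follow numerically.** All inputs here are assumptions. Let both arms have the same true event risk p, and let staff call a share a of events related in one arm and b in the other. Recorded risks are p × a and p × b, so the spurious difference is p × (a − b). With 80 randomized 1:1 there are 40 per arm.

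| p | a v b | Recorded | Difference | Expected patients of 40 |
|---|---|---|---|---|
| 20% | 60% v 40% | 12% v 8% | 4 points | 4.8 v 3.2 |
| 20% | 70% v 30% | 14% v 6% | 8 points | 5.6 v 2.4 |
| 40% | 60% v 40% | 24% v 16% | 8 points | 9.6 v 6.4 |
| 40% | 70% v 30% | 28% v 12% | 16 points | 11.2 v 4.8 |
| 60% | 60% v 40% | 36% v 24% | 12 points | 14.4 v 9.6 |
| 60% | 70% v 30% | 42% v 18% | 24 points | 16.8 v 7.2 |

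Swapping a and b reverses the sign. With equal attribution of 50% in both arms the difference is 0, but half of the events are lost from each arm. A real difference can also disappear: true risks of 60% v 40% with attribution of 40% v 60% are recorded as 0.60 × 0.40 = 24% v 0.40 × 0.60 = 24%.

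The table shows how the filter works. It does not estimate what happens in this trial.

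**The case against.** The strongest reply is that two sentences in a journal article summarize a longer protocol. The second concerns reporting to authorities, so the paragraph may describe what is passed on and not everything that is written down. Table 2 has no restriction, and event definitions and form fields are normally left to the full document. This reply stands in part: it cannot be said that unrelated events are in fact going unrecorded. It does not remove the point. The article states a restriction, which is different from leaving out a detail. If the full protocol records everything, Section 2.3.5 misdescribes it. If it does not, the rule needs changing.

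A reader might infer more than the text allows in five ways:

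- **That a planned safety comparison is biased.** Section 2.4.2 plans none. The concern applies to any summary by arm that is later built on these records.
- **That whoever assesses relatedness is known to be unblinded.** The article does not name this person. Knowledge of the drug is a strong inference from Sections 2.2 and 3.2, but it is not stated.
- **That harms would be invisible.** Creatinine, potassium, and office and 24-hour blood pressure are collected at visits 1 to 5 regardless of attribution, and investigator-initiated withdrawals are documented. Other clinical events have no comparable safeguard.
- **That the newer drug would attract more attributions.** Nothing in the article shows this, and both arms contain valsartan.
- **That the visit schedule adds to the bias.** Adverse events are marked at weeks 0, 4, 8, 26 and 52, leaving intervals of 26 − 8 = 18 and 52 − 26 = 26 weeks. But a visit can capture events since the last one, phone contacts fall at weeks 12 and 38, extra visits are allowed, and both arms follow the same schedule. The intervals create no difference between arms.

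**Conclusion.** The point holds as a defect in a stated rule. Section 2.3.5, followed as written, puts a relatedness judgement before recording, in a trial where that judgement is probably made with knowledge of the drug. Adverse-event counts by arm drawn from such records would reflect attribution as well as occurrence, and events first judged unrelated would not appear among them.

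This conclusion rests on two assumptions: that the sentence is applied literally, and that relatedness is judged by staff who know the allocation. The direction and size of any bias cannot be taken from the article, and the 4 to 24 points above depend entirely on assumed inputs. The primary endpoint, the sample size and the blinded CMR reading are unaffected. The change is worth making, but it does not threaten the trial's main result.

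**What to change.** Reword Section 2.3.5 so that all adverse events are recorded regardless of suspected relationship, with seriousness and causality as separate fields completed afterwards. Make this consistent with the unrestricted adverse-event row in Table 2. In the safety report, tabulate all events by arm and show related events as a subset.

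If the full protocol already works this way, only the article's wording needs correcting. If it does not, the cost is revised form wording and modest extra recording for 80 participants seen at one centre. New wording cannot recover events missed earlier. Recruitment began in June 2019, so if events were collected under the narrower rule, the safety report should say so and give the date of the change. The change concerns data capture only and alters no treatment rule.

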### Statistical consideration

2.4.

#### Sample size calculation

2.4.1.

We determined that a sample size of 35 participants per group would provide the trial with 80% power at a 5% significance level (two-sided) to detect an absolute minimum difference between treatment groups of 3.5 mL/m^2^ in terms of change in interstitial volume from baseline following 52 weeks, assuming an SD of 5.8 mL/m^2^ [data that was subsequently published (25)] and a moderate correlation of 0.60 between interstitial volumes at baseline and 1 year. The effect size was based on an estimate of the magnitude of myocardial fibrosis regression that could be expected to translate into improved clinical outcomes (5). The study plan is to randomize 80 participants, allowing up to 15% dropout and treatment discontinuation.

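### Randomizing 80 covers a 12.5% loss of endpoint scans, not the stated 15%; the effect on power is about one percentage point

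*Protocol article*

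**What the plan says.** Section 2.4.1 (Sample size calculation) states that "a sample size of 35 participants per group would provide the trial with 80% power" at a two-sided 5% level. The target is a between-group difference of "3.5 mL/m^2^ in terms of change in interstitial volume from baseline following 52 weeks". The variance inputs are given as "assuming an SD of 5.8 mL/m^2" and "a moderate correlation of 0.60 between interstitial volumes at baseline and 1 year".

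The section ends with the recruitment target: "The study plan is to randomize 80 participants, allowing up to 15% dropout and treatment discontinuation". No other reason is given for moving from 70 to 80.

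Three statements elsewhere bear on what a loss means:

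- Section 2.2: "Participants are randomized on an allocation ratio of 1:1", so losses are naturally counted per arm.
- Section 2.2: a participant who withdraws after more than 12 weeks of randomized treatment has all endpoint investigations at that time, unless not contactable, unwilling or deceased.
- Section 2.4.2: the analysis follows intention to treat and includes everyone in the assigned group.

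**The concern.** An allowance for loss has one job: to say how many randomized participants can be lost while the number behind the power statement is still reached. Here the three printed figures (70 needed, 80 randomized, up to 15% lost) should agree at the stated limit, and they do not.

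What is at stake is modest. The allowance is the figure a reader will use to judge whether attrition stayed within what the design was built to bear. If 11 or 12 of the 80 had no endpoint scan, the trial could be described as within its allowance while having fewer than the 70 participants on which its power was calculated.

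**Working it through.** **Inputs** (section 2.4.1; allocation from section 2.2): difference 3.5 mL/m²; SD 5.8 mL/m²; correlation 0.60; two-sided alpha 0.05; power 80%; 35 per group; 80 randomized 1:1; loss up to 15%.

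**Step 1. Reproduce the plan's 35 per group.** The SD of 5.8 is read as that of a single measurement, because a correlation is given with it.

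- SD of change = 5.8 × √(2 × (1 − 0.60)) = 5.8 × √0.8 = 5.188.
- n per group = 2 × (1.960 + 0.842)² × 5.188² / 3.5² ≈ 34.5, rounded up to **35**. This matches.
- Using 5.8 directly as the SD of change would give 44 per group, so the change-score reading is the one that fits the text.
- With the exact (noncentral) t distribution the answer is 36 per group, one more than stated. That is a difference of method, not an error.

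**Step 2. Apply the stated allowance to 80.**

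- 80 × 0.15 = 12 lost; 80 × 0.85 = 68 left, or **34 per group**. This is 2 short of 70.
- Loss that 80 can absorb: 80 − 70 = 10 participants; 10/80 = **12.5%**.
- Number needed to keep 70 after a 15% loss: 70/0.85 = 82.4, so 83. With equal arms, 35/0.85 = 41.2, so 42 per arm, or 84.

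**Step 3. Size of the effect on power.** By the normal approximation, power = Φ(3.5 / (5.188 × √(2/n)) − 1.960).

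- n = 35: Φ(2.822 − 1.960) = Φ(0.862) = 80.6%.
- n = 34: Φ(2.782 − 1.960) = Φ(0.822) = 79.4%.

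| Analysed per group | Normal approximation | Exact t |
|---|---|---|
| 40 (no loss) | 85.5% | 84.6% |
| 35 (plan's figure) | 80.6% | 79.5% |
| 34 (all 15% lost) | 79.4% | 78.3% |

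The comparison must stay within one column. From 35 to 34 per group the fall is 80.6 − 79.4 = 1.2 points, or 79.5 − 78.3 = 1.2 points, on these rounded values. Setting the exact-t 78.3% against the nominal 80% would mix in the half point by which the exact method already falls below 80% at 35 per group.

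**The case against.** The strongest defence is that the 15% is not a forecast of missing scans. It is an upper limit, and it pools dropout with treatment discontinuation. Under intention to treat, stopping the study drug does not by itself remove anyone from the analysis, and section 2.2 arranges endpoint scans for those who withdraw after more than 12 weeks. Of the 12 participants who make up 15% of 80, only two (one in each arm, if losses are balanced) need to supply an endpoint scan for 35 per group to be reached. This stands: 68 is a worst case, not the expected number analysed. It does not fully rescue the sentence. Section 2.2 makes exceptions, does not provide for scans after withdrawal at 12 weeks or earlier, and an early scan is not a 52-week scan. If discontinued participants are expected to contribute data, the allowance is counting something other than what determines power.

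A reader might go further and infer any of the following. The document does not support them.

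- *That the 80% power is wrong.* It is attached to 35 per group, where it reproduces. The article nowhere says that 80% is kept at exactly 15% loss.
- *That a loss between 12.5% and 15% would be wrongly accepted under some rule.* No decision in the article turns on the loss rate; the allowance is only a descriptive benchmark.
- *That 80 came from adding 15% to 70* (70 × 1.15 = 80.5). This is possible, but the derivation is not shown, 80.5 would round up to 81, and the point does not need it.

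**Conclusion.** The point holds as a minor inconsistency. At the stated limit, and if everyone in the allowance lacks an endpoint CMR, the 80 randomized leave two fewer than the 70 behind the power statement; the loss that fits is 12.5%. The cost in power is about 1.2 points on either method, and both values at 34 per group stay within 2 points of the stated 80%.

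This rests on three assumptions: the change-score reading of the SD, which the match at 35 per group supports; losses split evenly between arms; and no usable endpoint scan from any of the 12. If some of the 12 are scanned, the shortfall shrinks or disappears. It would be wrong to conclude that the trial is materially underpowered: with all 80 analysed, power is about 85%, and error in the assumed SD or correlation could easily outweigh a one-point change.

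**What to change.** Change one sentence in section 2.4.1, in one of two ways:

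1. Keep 80 and restate the allowance as up to 12.5% (10 participants) without an endpoint CMR, which leaves 35 per group. Say explicitly that the allowance now counts missing endpoint scans rather than treatment discontinuation, since this changes what is being counted.
2. Keep 15% and add that, if none of those participants has an endpoint CMR, 34 per group remain and power is about 78–79%.

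The first is preferable because it ties the allowance to the quantity that determines power. Neither needs more participants or any change to the design or analysis; the only cost is a slightly less generous stated allowance, or a stated power just under 80%. Raising enrolment to 83 or 84 would also make the figures agree, but is out of proportion to a one-point difference.

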#### Statistical analysis

2.4.2.

The analyses will be based on the intention-to-treat principle, such that all participants will be included in analysis according to their assigned treatment groups.

Baseline characteristics and changes in CMR endpoints between the two treatment groups will be compared. If significant baseline differences are found between the two groups, appropriate modifications to analytical methods may be made to adjust for the differences. Categorical variables will be compared with *χ*^2^ test and described as count (percentage). Continuous variables that are normally distributed will be compared using the parametric Student’s *t*-test and presented as mean ± SD. If the normality assumption is not met, they will be compared using the non-parametric Mann–Whitney *U* test and described as median (interquartile range). All analyses will be performed two-sided at the 5% significance level. A *p*-value of <0.05 will be considered statistically significant. Additional exploratory analyses may be performed.

Statistical analyses will be performed using SPSS (IBM SPSS Inc., NY, USA) and GraphPad Prism (GraphPad Software, Inc., CA, USA).

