**Methods:**

Role of ARNi in Ventricular Remodeling in Hypertensive LVH (REVERSE-LVH) is a prospective, randomized, open-label, blinded endpoint (PROBE) clinical trial. Adults with hypertension and left ventricular hypertrophy (LVH) according to Asian sex- and age-specific thresholds on cardiovascular magnetic resonance (CMR) imaging are randomized to treatment with either sacubitril/valsartan (an ARNi) or valsartan (an ARB) in 1:1 ratio for a duration of 52 weeks, at the end of which a repeat CMR is performed to assess differential changes from baseline between the two groups. The primary endpoint is the change in CMR-derived diffuse interstitial fibrosis volume. Secondary endpoints include changes in CMR-derived left ventricular mass, volumes, and functional parameters. Serum samples are collected and stored to assess the effects of ARNi, compared with ARB, on circulating biomarkers of cardiac remodeling. The endpoints will be analyzed with reference to the corresponding baseline parameters to evaluate the therapeutic effect of sacubitril/valsartan vs. valsartan.

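### The primary endpoint is tested by an unadjusted comparison of change, with baseline adjustment left to a baseline significance test, at a cost of about 20% of the variance

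*Protocol article*

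**What the plan says.** The abstract (Methods) defines the endpoint: "The primary endpoint is the change in CMR-derived diffuse interstitial fibrosis volume". Section 2.4.2 compares changes in the CMR endpoints between arms and gives the test: "Continuous variables that are normally distributed will be compared using the parametric" Student's t-test, with Mann–Whitney U if normality fails. Neither test uses the baseline value as a covariate.

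The only provision for adjustment in section 2.4.2 is this: "If significant baseline differences are found between the two groups, appropriate modifications to analytical methods may be made to adjust for the differences". It has a significance trigger, permissive wording on whether to act, and no named method or covariate.

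Section 2.4.1 sets the sample size at 35 per group "to detect an absolute minimum difference between treatment groups of 3.5 mL/m^2^ in terms of change in interstitial volume from baseline following 52 weeks". Its other two inputs are a standard deviation (5.8 mL/m²) and "a moderate correlation of 0.60 between interstitial volumes at baseline and 1 year". The abstract also says that endpoints will be analysed by reference to baseline. That wording fits a change score and specifies no adjusted model.

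**The concern.** Under randomisation, any baseline difference between arms is due to chance, so a significance test of it answers no useful question. Whether to adjust should depend on how strongly baseline predicts the 52-week value, and the plan itself assumes a correlation of 0.60.

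At that correlation a change score over-corrects. It subtracts the whole baseline value when only 0.60 of it carries forward. If the arms differ by D at baseline, the difference in change is expected to shift by −(1 − 0.60)D = −0.4D with no treatment effect at all. The rule leaves that shift in place whenever the baseline test is non-significant, which is about 95% of the time.

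Three things are at stake: precision that could be had at no cost, a primary estimate that depends on which arm happened to start higher, and an analysis method that can be chosen after the data are seen. The last matters more here because treatment is open-label and only the CMR reading is blinded.

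**Working it through.** **Inputs** (sections 2.4.1 and 2.4.2): difference 3.5 mL/m²; SD 5.8 mL/m²; correlation r = 0.60; two-sided 5%; 80% power; 35 per group. The SD is taken as the between-patient SD at one visit and as equal at both visits. The plan does not say so, but of the three readings tried in step 1 only this one, with a change-score test, returns its sample size.

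**Step 1. Reproduce the plan's figure.** n per group = 2 × (1.960 + 0.842)² × SD² / 3.5².

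| Analysis | SD used | n per group |
|---|---|---|
| Change score | 5.8 × √(2 × (1 − 0.60)) = 5.19 | 34.5 → 35 |
| SD of 5.8 without the correlation | 5.8 | 44 |
| ANCOVA on baseline | 5.8 × √(1 − 0.60²) = 4.64 | 27.6 → 28 |

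Only the change score gives 35, so the trial is sized for the unadjusted test.

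**Step 2. Precision.** Residual variance is 4.64² = 21.53 for ANCOVA against 5.19² = 26.91 for change. The ratio is (1 + r)/2 = 0.80, a 20% reduction.

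| At 35 per group | Change-score t-test | ANCOVA |
|---|---|---|
| Power (noncentral t) | 79.5% | 87.5% |
| Power (normal approximation) | 80.6% | 88.4% |
| 95% CI half-width, mL/m² | 2.47 | 2.21 |

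**Step 3. Size of the uncorrected shift.** The standard error of the baseline difference is 5.8 × √(2/35) = 1.39 mL/m². The baseline test is therefore non-significant up to 1.996 × 1.386 = 2.77 mL/m². The largest shift left unadjusted is 0.4 × 2.77 = 1.11 mL/m², and 1.11/3.5 = 32%. Across all trials with a non-significant baseline difference, the median absolute shift is 0.35 mL/m² (10% of 3.5) and the mean is 0.40 (11%).

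**Step 4. Simulated behaviour** (35 per group, normal data; separate runs of 20,000 to 100,000 trials, which agree closely). The plan's rule is simulated as ANCOVA whenever baseline p < 0.05 and the change-score test otherwise. That is a generous reading, since the plan names no method and does not require the adjustment.

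| | Change score | Plan's rule | ANCOVA always |
|---|---|---|---|
| Overall type I error | about 5% | about 4.5% | about 5% |
| Overall power | 79.6% | 80.3% | 87.0% |

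For trials with baseline p between 0.05 and 0.10, which the rule leaves unadjusted:
- With no true effect, the change-score test rejects in 9.5% to 9.7% of trials and ANCOVA in 5.1% to 5.3%.
- With a true difference of 3.5, change-score power is about 50% or 96%, depending only on which arm started higher. ANCOVA gives about 86% either way.

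**Step 5. Sensitivity to the correlation.** The variance saving is 25% at r = 0.50, 15% at 0.70 and 10% at 0.80. At r = 0.50 and 35 per group, power is 70% for the change score and 82% for ANCOVA.

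**The case against.** The strongest reply is that nothing is invalid. A t-test on change is unbiased over randomisations and holds its type I error at about 5%. It is also the test the sample size was built on, and it delivers roughly the 80% power promised. The conditional rule, if applied mechanically, is slightly conservative. All of this stands.

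The larger figures also need context. The 9.5% rejection rate belongs to a band holding about 5% of null trials; across all trials with a non-significant baseline difference the rate is 4.5%. The 32% shift is the extreme, and only about 2.4% of those trials shift by more than 1.0 mL/m². The rule does permit adjustment for the largest imbalances. The 20% saving is exact only at r = 0.60 with equal SDs.

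It can also be said that an article leaves the choice of model to the analysis plan. That holds for the details of a model, but not here: section 2.4.2 states both the test and the trigger for adjustment, so this is a rule that was set, not a detail left open.

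**Conclusion.** The concern holds. The plan fixes an unadjusted primary test and ties adjustment to a baseline significance test that carries no relevant information, leaving both the decision and the method to discretion. On its own assumptions this forgoes a 20% variance reduction: 79.5% against 87.5% power at 35 per group, or 35 against 28 participants per group for the same power. Applying the rule instead of adjusting always recovers less than one percentage point (80.3% against 79.6%).

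This is not a claim of inflated overall type I error or of a trial underpowered for its stated test. The case rests on lost precision, on sensitivity to a chance imbalance of up to 1.11 mL/m² (typically about 0.35), and on a primary analysis that is not fixed in advance. The figures assume r = 0.60, equal SDs of 5.8 mL/m² at both visits and approximately normal data. If the true correlation is below 0.60, the case for ANCOVA is stronger.

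**What to change.** In section 2.4.2:
- Make the primary analysis an ANCOVA of week-52 indexed interstitial volume (or its change, which gives the same treatment estimate) on treatment and baseline interstitial volume, fitted in all cases. Report the adjusted mean difference with its 95% CI.
- Use the same model for each CMR secondary endpoint, with that endpoint's own baseline.
- Let the ANCOVA replace both the t-test and the Mann–Whitney route for these endpoints, and state in advance what will be done if the residuals are clearly non-normal.
- Delete the conditional adjustment rule and the significance tests of baseline characteristics; describe the baseline by arm instead.

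The cost is a change of wording. Baseline CMR is already scheduled for everyone, and SPSS, which the plan names, fits the model. Because recruitment began in June 2019 and treatment is open-label, the change should be a dated amendment made before any outcome data are examined by arm. The sample size can stay at 35 per group, with the extra precision kept as a margin against a correlation below 0.60.
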